## Abstract

**Introduction:**

Post-stroke fatigue (PSF) is an abnormal, persistent, and unexplained physical and psychological tiredness in patients after stroke. It is a common symptom of stroke patients with poor quality of life and bleak prognosis, and the incidence rate is up to 39% to 72%. It has been widely reported that medicine treatments achieved a lot of progress, there still needs to develop more powerful new strategies to more powerful effect. The transcranial direct-current stimulation (tDCS) shows great potential for the treatment of PSF. This study proposes to apply a double-blind randomized controlled clinical trial to explore the effect and safety of tDCS combined with routine rehabilitation for PSF.

**Methods and analysis:**

One hundred patients with PSF will be randomly divided into two groups. One of the groups will receive conventional rehabilitation therapy and active tDCS, whereas another group will receive conventional rehabilitation treatment and sham tDCS. Both groups will receive the intervention for 4 weeks, during which time they will undergo either active or sham tDCS 20 min a day, 6 days a week. Primary outcome: Fatigue Severity Scale (FSS) will be measured at baseline every weekend during the intervention period. Secondary results: Fatigue Impact Scale (FIS), Functional Assessment Chronic Illness Therapy (Fatigue) (FACIT-F), and Specialized Quality of Life Scale in Stroke (SS-QOL) will be measured at baseline and at the end of the intervention time of 4 weeks. Throughout the study, adverse events and adverse reactions will be measured during every treatment. The research study “Effects of transcranial direct current stimulation on patients with post-stroke fatigue” has been approved by the Ethics Committee of the First Affiliated Hospital of Nanchang University: Clinical Medicine Ethics Review [2015]043 in Nov 2015.

**Discussion:**

This study will provide insight into the efficacy of transcranial direct-current stimulation for post-stroke fatigue. This is a double-blind randomized controlled trial whose aim is to assess the effects of tDCS on PSF. This study can provide more information about the treatment of PSF. This study has a period of follow-up, which allows for greater accuracy. It is a single-center trial, and this may be a limitation. The other limitation of this study is the relatively small number of participants; thus, the influence of chance on experimental results cannot be completely ruled out.

**Trial registration:**

Chinese Clinical Trial Registry ChiCTR2000031120. Registered on March 22, 2020. This protocol version number is V1.1.

## Introduction

### Background and rationale

Fatigue is defined as the decrease in physical and/or mental performance that results from changes in central, psychological, and/or peripheral factors [1]. Post-stroke fatigue (PSF) is defined as observable and measurable performance degradation that occurs during the repetition of a physical or mental task. It is an early feeling of exhaustion, boredom, and aversion to effort. PSF was first mentioned in 1999 and has been evaluated separately by the medical community to distinguish it from other post-stroke psychosocial disorders. According to previous studies, 39–72% of stroke survivors have PSF.

Descriptions of fatigue include different aspects of the phenomenon, problems related to self-control and emotional instability, reduced mental capacity, and energy requirements for daily activities, such as reading and participating in physical or social activities. Fatigue can be divided into objective fatigue and subjective fatigue. And PSF is often referred to as subjective fatigue.

As for the characteristics of fatigue, PSF is qualitatively different from pre-stroke fatigue that may be exacerbated by stress and physical activity while responding well to rest, sleep, and hypothermia. The pre-stroke fatigue aggravated by physical activity is also known as exercise-induced fatigue. Exercise-induced fatigue is acute, with rapid onset, short duration, and a short recovery period. It usually occurs after vigorous physical exercise or the use of mental work. PSF, on the other hand, is chronic, long-lasting, and difficult to recover from. It can occur in the persistent activities of daily life such as taking a shower.

About the pathogenesis of PSF, repeated exhaustive exercise could result in up-regulation of the expression of mGluR1 and mGluR5 in the cortex M1 zone of rats suggesting that M1, with different time effects, contained important receptors related to the production of exercise fatigue. A transcranial direct-current stimulation (tDCS) of M1 and dorsolateral prefrontal cortex (DLPFC) significantly increased brain excitability in the M1 for at least 30 min [1]. Therefore, it suggests that we can improve fatigue by tDCS on the DLPFC.

TDCS is a noninvasive brain stimulation method that regulates cortical excitability by applying 1–2 mA direct current through the scalp. It requires at least one stimulator, electrode, and return electrode to loop. It can be divided into anode and cathode stimulation modes. By using tDCS to stimulate the motor cortex, it was found that anode stimulation can improve cortical excitability [2], whereas cathode stimulation can reduce cortical excitability. Furthermore, the effect of it is not only limited to the stimulated area, but also involves nearby brain regions [3] and can change the functional connectivity between brain regions [4]. If the time and intensity of stimulation are enough, the change of cortical excitability after a single stimulation can last for about 1 h [5] In the previous experiments [6], tDCS was found to improve fatigue using sham-controlled crossover designs, with between 10 and 25 participants and five tDCS treatment sessions using a motor, sensory, or dorsolateral prefrontal cortex (DLPFC) montage [6, 7]. The most recent study by Chalah et al. demonstrated that the DLPFC (left anodal) when compared to the posterior parietal cortex led to the highest fatigue-specific improvements.

One of the advantages of tDCS is that it can be regulated by the experimenter actively. Compared with transcranial magnetic stimulation, it is obvious that tDCS has a lower resolution. Conversely, it is less expensive, portable, and easier to use. More importantly, it was found that it has no side effects other than a slight tingling sensation.

Recently, tDCS is increasingly being used in many fields, such as dysphagia, head injuries, Alzheimer’s disease, Parkinson’s disease, acute and chronic pain, tinnitus, and depression. It is also being tested on healthy people [8]. However, few clinical studies have reported a combination of tDCS and PSF recovery.

### Objectives and hypotheses

The objectives of this randomized controlled trial are as follows:
To study the efficacy of tDCS in combination with conventional rehabilitation;To evaluate the safety of tDCS stimulation in patients with PSF; andPresentation of the research plan and the results of previous clinical trials to ensure compliance with previously recommended guidelines.

### Trial design

The clinical study is a prospective, randomized controlled trial designed with double-blinded assessments. Since there is no clinically effective treatment, we will perform the superiority test. This study will be carried out with 100 hospitalized patients with PSF. All participants will be randomly allocated to either the intervention or control group in a 1:1 ratio. Each group will, therefore, be composed of 50 patients. Interventions in both parallel groups were identical except for effective tDCS treatment. The control group will receive conventional rehabilitation combined with sham tDCS treatment, whereas the intervention group will receive conventional rehabilitation combined with active tDCS treatment. This trial will be composed of a 4-week intervention and an 8-week follow-up period. From the first to the fourth week, the primary outcome Fatigue Severity Scale (FSS) will be measured at baseline on every weekend. The secondary outcomes Fatigue Impact Scale (FIS), Functional Assessment Chronic Illness Therapy (Fatigue) (FACIT-F), and Specialized Quality of Life Scale in Stroke (SS-QOL) will be performed at the end of the intervention period. Adverse events and untoward effects will be supervised in each treatment. The first affiliated Hospital of Nanchang University (NCU), which will undertake the study, is responsible for training rehabilitation therapists on the standard operating procedure and supervising the progress of this trial at all clinical sites. In addition, the randomization and blinding will be performed by an independent statistician from the Center of Evidence Based Medicine, NCU. A flow diagram of this trial is presented in Fig. 1.

**Fig. 1 Fig1:**
[figure not shown]
Flow diagram of the trial design. tDCS, transcranial direct current stimulation; PSF, post stroke fatigue

## Methods

### Study setting

Participants will be recruited from the intensive-care unit of First Affiliated Hospital. With informed consent, potential participants will be screened by neurologists at the Neonatal Intensive Care Unit of the First Affiliated Hospital of Nanchang University based on inclusion and exclusion criteria. The patients who are eligible for this study are those who meet all the requirements. Eligible individuals will be assessed by a neurologist for diagnosis and given a rehabilitation assessment. All study participants will be required to provide informed consent for themselves and their family members.

### Eligibility criteria

Patients who meet the following criteria will be considered eligible to participate in the trial:
Stroke appeared at least 3 months ago and within 1 year, to ensure that they are not in the acute phase of stroke.Apparent fatigue, decreased energy, need for increased rest time, or fatigue out of proportion to physical activity.One of the following is true (FSS average score is more than 4):Sleep or rest is difficult to achieve or recover,Motivation is retained and productivity is reduced,Self-perception is required to overcome this lack of vitality,Fatigue affects daily life/tasks,Fatigue lasts for several hours after exercise,Fatigue is a significant concern,(4)Male or female patients aged 18–65 years.(5)By magnetic resonance imaging (MRI), patients with no significant head displacement, structural damage, extensive necrosis of the brain structure, no significant pyramidal tract necrosis or thalamic injury in the brain stem, and not more than 30% of each lobe damaged on one side of the brain.(6)The patient’s condition and vital signs are stable, and the patient's family voluntarily participated in the trial and signed an informed consent form.(7)The patient has no other serious complications, such as respiratory failure, acute heart failure, severe pulmonary infection, and upper gastrointestinal bleeding.

Patients who met the following criteria would be excluded from the trial:
Sedatives, anesthetics, psychoactive drugs, muscle relaxants, or Na+ and Ca2 + channel blockers, such as carbamazepine, will be administered during the evaluation period.The patient relies on inhalers.The course of disease is more than 1 year.There are any contraindications, such as pacemaker, denture, and metal prosthesis.There is an epilepsy or seizure history confirmed by EEG.Serious diseases such as heart, liver, and kidney failure.Progressive nervous system diseases, such as the central nervous system or degenerative diseases.The patient has a fever.The patient has a local skin injury or inflammation. The patient has hemostasis, coagulation, or anticoagulation dysfunction. Acute large area cerebral infarction. High sensitivity of pain stimulation area. Brain injury, brain parasitosis, or brain tumor. Hemiplegia or dysfunction of limbs (patients with a Fugl-Meyer scale score below 85). Accompanied by aphasia. Patients with incomplete clinical data and poor compliance. Accompanied with serious organ disease, endocrine disease, and mental illness. Patients with a score of 10 or more on the PHQ-9 scale.

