#### Active tDCS

The intervention group participants will be treated with active tDCS. We will place the anode of the electrode in the dorsolateral prefrontal cortex (DLPFC) on the left side of the patients’ forehead, and cathode in the superior margin of the right orbit. The current intensity will be 1.5 mA according to the previous article [10]. The diameter of the electrode plate is 5cm. The unit type is MBM-I (Jiangxi Huaheng Jingxing Medical Technology Co., LTD, Nanchang City, Jiangxi Province, China). The treatment parameters will be 20 min per session, once a day, and 6 times a week. Patients will receive tDCS treatment alone, not at the same time as other treatments. The treatment will be carried out in the neuromodulation room, at the appointed time, by a specialized therapist.

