### Trial outcomes

#### Outcome measures

In this study, primary outcomes will be measured at baseline and at the end of every week from the 1st to the 4th week. Secondary outcomes will be measured at baseline and the end of the 4th week. During each treatment, adverse events and untoward effects will be assessed. All outcome assessments will be independently performed by experienced and blinded assessors, the same one professional rehabilitation physician. A summary of all the measures in the trial is shown in Table 1.

**Table 1 Tab1:** Data on the design of the study

Point in time	Screening stage	Treatment period 1 (1 week)	Treatment period 2 (2 weeks)	Treatment period 3 (3 weeks)	Treatment period 4 (4 weeks)
Informed consent	**×**				
Inclusion and exclusion criteria	**×**				
Withdrawal, drop out, and termination criteria		**×**	**×**	**×**	**×**
Basic information	**×**				
Past medical history	**×**				
Therapeutic parameter record		**×**	**×**	**×**	**×**
**(*****Baseline*****) Fatigue Severity Scale (FSS)**	**×**	**×**	**×**	**×**	**×**
**Functional Assessment Chronic Illness Therapy (Fatigue) (FACIT-F)**	**×**				**×**
**Fatigue Impact Scale (FIS)**	**×**				**×**
**Specialized Quality of Life Scale in Stroke (SS-QOL)**	**×**				**×**
Overall efficacy evaluation					**×**
Complications	**×**	**×**	**×**	**×**	**×**
**Adverse events recorded**	**×**	**×**	**×**	**×**	**×**

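### The only exclusion that names seizures depends on EEG confirmation, so a clinical seizure history without it does not by itself bar entry

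*Protocol article*

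**What the plan says.** Among the exclusions under Eligibility criteria, one item names epilepsy or seizures: "There is an epilepsy or seizure history confirmed by EEG". The same list excludes patients given sedatives, anesthetics, psychoactive drugs, muscle relaxants or channel blockers; its last part reads "Na+ and Ca2 + channel blockers, such as carbamazepine, will be administered during the evaluation period". It also has an open-ended contraindications item, illustrated by a pacemaker, a denture and a metal prosthesis.

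The inclusion criteria admit patients by time since stroke: "Stroke appeared at least 3 months ago and within 1 year". Study setting says that neurologists do the screening.

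On the intervention, Background and rationale states that "anode stimulation can improve cortical excitability". The section on active tDCS makes the montage anodal: "We will place the anode of the electrode in the dorsolateral prefrontal cortex (DLPFC) on the left side of the patients’ forehead". Sessions are given six times a week for 4 weeks, which is 6 × 4 = 24 sessions. Objectives and hypotheses lists the safety of tDCS in these patients as an aim.

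Table 1 has screening rows for "Inclusion and exclusion criteria" and "Past medical history".

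**The concern.** A seizure exclusion in a stimulation trial is there to keep out patients with a known susceptibility. The wording here adds a qualifier that makes the exclusion narrower than that purpose. A seizure history is a past clinical event, whereas EEG confirmation is a separate test result that a patient may or may not have. Tying the first to the second means that a negative or missing test keeps a patient eligible under this item.

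The article supplies the reason why this matters: it describes the active treatment as raising cortical excitability and gives it repeatedly to people with a stroke in the past year. Two things are at stake. One is the protection of the individual patient. The other is the safety conclusion: with 50 patients per arm, one seizure in a patient who had had one before could not be cleanly attributed either to stimulation or to prior susceptibility.

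**Working it through.** The article gives no figure on this point, so the check is a reading of the criteria against one another.

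**Step 1: two readings of the item.**
- Reading A: EEG confirmation qualifies both epilepsy and seizure history. Any patient without a confirming EEG, including one with clinically diagnosed epilepsy, falls outside the item.
- Reading B: epilepsy excludes in any case, and EEG confirmation qualifies only seizure history. Diagnosed epilepsy is then covered, but a patient with a clinical seizure, no epilepsy diagnosis and no confirming EEG still falls outside.

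A gap remains on both readings; B makes it smaller.

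**Step 2: do other criteria close it?**
- Drug exclusion: it acts on patients given the listed drug classes during the evaluation period. It may catch some who are treated after a seizure. It does not reach a patient on no such drug.
- Contraindications item: the wording is open, so a screener may use it. Its examples are devices and metal, and seizures have their own, narrower item, which a screener would naturally apply first. It permits exclusion but does not require it.
- MRI limits and the brain-injury item: these concern structural damage, not seizures.
- Screening by neurologists: this allows clinical judgement, but no written rule obliges them to exclude.

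What remains is an untreated patient with a clinical seizure history and a normal or absent EEG. No criterion requires that this patient be excluded.

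**Step 3: set against the stated purpose.** Background and rationale says of the motor cortex that "it was found that anode stimulation can improve cortical excitability". The active arm uses anodal stimulation, and safety is an objective. A criterion that leaves out part of the seizure history does not fit these statements well.

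**Step 4: consequence for the safety comparison.** The article plans a chi-square or Fisher test for adverse events. Suppose one seizure occurs among 100 patients, 50 per arm. With no treatment effect, the chance that it falls in the active arm is 50/100 = 0.5, and the two-sided Fisher p-value is 0.5 + 0.5 = 1. The test cannot inform such an event. Its interpretation would rest on the case itself, and a prior seizure would be the competing explanation.

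**Step 5: number affected.** The expected count is the number randomised, times the proportion with a clinical seizure history, times the share of those without EEG confirmation, times the share not removed by other criteria. Only the first term (100) is in the article.

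**The case against.** The best defence is that the criteria work as a set and are applied by neurologists. The contraindications item is open-ended, the drug exclusion is wide (sedatives and psychoactive drugs as well as channel blockers), and on reading B diagnosed epilepsy is excluded outright. What remains may be a small group. That stands as a limit on the size of the problem, but these routes are discretionary or partial, and the written rule can be applied differently from one screener to the next.

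Three stronger inferences are tempting and should not be drawn.
- A reader might take the lack of an EEG row in Table 1 to mean that no EEG is done. The table itemises no eligibility test: MRI, PHQ-9 and Fugl-Meyer are also required and also have no row. EEG may fall under the general eligibility row, and under Recruitment patients are found through the computer record system, where an earlier EEG could be held. The missing row is not evidence.
- A reader might put in assumed rates and arrive at a few patients per 100. Neither the seizure rate nor the share without EEG confirmation is in the article, and such a figure would ignore the other exclusions.
- A reader might call a seizure in such a patient a predictable effect of tDCS. The article says that anodal stimulation raises excitability. It does not say that it provokes seizures, and it reports no side effect beyond slight tingling.

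It could also be said that a condensed article leaves such detail to the full protocol. That would answer an omission. Here the published text states a restrictive qualifier.

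**Conclusion.** The point holds as a wording defect in a safety exclusion. On either reading, an untreated patient with a clinical seizure history and a normal or absent EEG does not meet the one criterion that names seizures, and no other criterion requires that patient's exclusion. It does not follow that such patients must be enrolled, because screeners have discretion to refuse them.

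The number affected cannot be estimated from the documents. The conclusion rests on a literal reading of the published criterion and on the article's own account of anodal stimulation; it needs no assumed rate. The sample size calculation and the efficacy analysis are not affected. The change is worth making because it bears on patient protection and on the safety objective, and it costs little.

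**What to change.** Reconcile the criterion with its safety purpose by rewording it so that EEG confirmation is not a necessary condition. One way is to let a seizure history recorded in the past medical history at screening count, with an EEG finding as an additional ground. The new wording should also settle whether any EEG qualifier applies to epilepsy, to seizure history or to both. The exact clinical threshold is for the investigators to set.

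The cost is one phrase in the eligibility criteria and the matching line on the screening form. Past medical history is already collected at screening, so no procedure is added. The downside is that a few more screened patients become ineligible.

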### Study endpoints

The endpoints of the study are as follows:
In the event of a serious adverse reaction during the course of the test, the test will be terminated in time to protect the subject.In the event of a serious complication or deterioration in the course of the test, the test will be terminated.The test will be terminated if the subject is asked to withdraw from the clinical study.And if the patient does not cooperate and does not receive treatment and the therapist’s explanation is not working, then the study will be suspended.

The researchers will keep detailed records of why and when the subjects quit the study.

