### Statistical methods

#### Statistical analysis

Statistical methods using statistical analysis software SPSS21.0 will be used to analyze the test results. In the descriptive analysis of samples, the continuous variables are expressed in mean and standard deviation for the data of normal distribution and in the range of median and quartile for the data of non-normal distribution. The normally distributed packets are compared statistically between the *t* test groups. The ordinal level variables of the non-normal distribution are compared statistically with the Mann-Whitney *u* test. Measures with discrete distributions will be expressed as percentages and analyzed using accurate tests of either chi-square *Χ*^2^ or Fisher, as appropriate. If necessary, we will use the general linear model or logit model to adjust for confounding effects.

We will use the *t* test or the Mann-Whitney test to compare baseline characteristics between the different groups. If there is statistical significance, inequality will be treated as a confounding factor in the final efficacy analysis. In order to compare one-time or two-time results between groups, the continuous data will be analyzed by *t* test or non-parametric test, and the data will be analyzed by Pearson chi-squared or Fisher precision test. In order to control the possible confounding variables, linear models or linear regression models will be used for dependent continuous variables and dependent classified variables. The subgroup analysis of the main results will be stratified according to the sex of the participants. Analysis of variance will be used to repeat the measurement data. The analysis of primary and secondary outcomes will be based on intention-to-treat (ITT) and a per-protocol (PP) basis. The results of the ITT analysis will be compared with those of the PP analysis to determine if they are consistent. The missing data will be treated as the last carrier of observation. Adverse events will be listed and analyzed using either a chi-square test or Fisher’s precision test.

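### Exclusions with no time limit permit removal of randomised patients, and stopping treatment is treated as leaving the study, which weakens the ITT comparison

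*Protocol article*

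**What the plan says.** All references are to the protocol article.

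- **Eligibility criteria.** The exclusion list opens with "Patients who met the following criteria would be excluded from the trial". It names no time point. Among its entries are "Patients with incomplete clinical data and poor compliance" and a group of sedating, psychoactive and channel-blocking drugs that "will be administered during the evaluation period". The evaluation period is not defined.
- **Study setting and Outcome measures (Table 1).** Candidates are screened against the criteria. The Table 1 row "Inclusion and exclusion criteria" is marked at the screening stage only. A separate row for withdrawal, drop-out and termination is marked in treatment weeks 1 to 4.
- **Basic treatments.** Drug use during the trial is left to the clinician for each patient.
- **Study endpoints.** Participation ends for a serious adverse reaction, a serious complication or deterioration, or withdrawal. It is suspended "if the patient does not cooperate and does not receive treatment" and the therapist's explanation fails. The section closes by requiring a record of why and when subjects quit. It does not say whether FSS assessment continues.
- **Statistical analysis.** "The analysis of primary and secondary outcomes will be based on intention-to-treat (ITT) and a per-protocol (PP) basis". The two results are to be compared for consistency, and missing data are filled with the last observation.
- **Ethics approval and consent to participate.** Participants are asked on the consent form whether their data may be used if they withdraw.

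**The concern.** There are two weak points.

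First, treatment runs to 24 sessions (6 a week for 4 weeks). Compliance with those sessions, completeness of the trial data and drugs given later are all things that can be observed after allocation. An exclusion list that names them without a time limit can be used to take out patients who have already been randomised.

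Second, the plan does not separate stopping stimulation from leaving the study. The listed reasons for stopping (adverse reaction, deterioration, refusal of treatment) are ones that could differ between active and sham stimulation and could be linked to fatigue. If outcome collection stops with treatment, the week-4 FSS is lost for the patients in whom an ITT comparison differs most from a per-protocol one.

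At stake is whether the result labelled ITT keeps the protection of randomisation. It also matters for the planned ITT versus per-protocol comparison, which is informative only to the extent that the ITT result contains real outcomes for patients who stopped.

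**Working it through.** The plan gives no figure on this point, so the main check sets the sections side by side.

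**1. Can the exclusions act after randomisation?**
- Pointing to no: Table 1 marks the criteria at screening only and handles withdrawal in its own row.
- Pointing to yes: the list's opening sentence excludes from the trial, not from enrolment. The drug criterion is written in the future tense about an undefined period. The Basic treatments section lets clinicians prescribe as needed, so a randomised patient could meet the drug criterion through ordinary care. No basis for judging poor compliance at screening is given.
- Result: removal after randomisation is permitted by the wording, but it is not prescribed.

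**2. What happens to a patient who stops treatment?**
- Study endpoints ends participation and records the reason and the date.
- Data collection and management describes ward visits, recall and telephone contact for patients who do not attend. It does not say that patients terminated under Study endpoints are still assessed.
- Statistical analysis then carries the last observation forward. FSS is taken at baseline and at the end of weeks 1 to 4. A patient stopped in week 3 before that week's assessment would therefore enter week 4 with the week-2 score, and a patient stopped in week 1 with the baseline score, that is, with no change.
- The direction of the error is not fixed. Carrying a score forward hides worsening in a patient stopped for deterioration, and it hides any later improvement in a patient stopped for other reasons.

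**3. How large could the effect of removal be?** The documents give no removal rates, so the following rests on assumptions. Suppose a fraction p with the worst outcomes is removed from one arm, outcomes are normal, and losses in the other arm are unrelated to outcome. The mean of the remaining patients shifts by φ(z_p)/(1 − p) SD. If removal is only correlated with outcome at r, the shift is multiplied by r.

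| p removed | φ(z_p) | Shift, r = 1 | Shift, r = 0.5 |
|---|---|---|---|
| 10% | 0.1755 | 0.1755/0.90 = 0.195 SD | 0.10 SD |
| 15% | 0.2332 | 0.2332/0.85 = 0.274 SD | 0.14 SD |
| 20% | 0.2800 | 0.2800/0.80 = 0.350 SD | 0.17 SD |

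For scale, 43 per group with two-sided α = 0.05 and 90% power detects √(2/43) × (1.960 + 1.282) = 0.70 SD. The shifts are then 0.10/0.70 = 14% to 0.35/0.70 = 50% of that difference.

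Two limits apply. The 0.70 SD is solved backwards from the stated 43, which the Sample size section's own inputs do not give: with a difference of 19.7 and a root-mean-square SD of √((4.54² + 9.58²)/2) = 7.50, the formula yields 2 × (1.960 + 1.282)² × 7.50²/19.7² = 3.04, or 4 per group. That is a separate matter. Also, the table describes deletion from the analysis. It does not measure the error from carrying scores forward, for which the documents give no basis.

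**The case against.** The strongest case for the plan is that its timing is stated. Table 1 and Study setting put eligibility at screening, and Randomization and allocation concealment speaks of allocating eligible participants. Recruitment works from medical records, so incomplete clinical data may simply mean an incomplete record. Poor compliance may be a judgement made at screening, and the evaluation period may be the assessment before treatment. Carrying the last observation forward keeps stopped patients in the ITT set, because everyone should have a baseline FSS. Data collection and management makes real efforts to complete outcome assessment. The definitions of the analysis sets may stand in the analysis plan that the section names, so their absence from an article is no fault.

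Most of this stands, and it limits the point. A reader might infer that these criteria can be known only after allocation, that randomised patients will in fact be removed, that ITT is impossible in practice, or that the ITT versus per-protocol check is empty. The documents do not support any of these. The criteria have plausible screening readings, no section says that such patients are dropped from ITT, and a stopped patient can be in ITT with a carried-forward score while left out of per-protocol, so the two sets can differ.

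Two things are not answered. The screening readings have to be supplied by the reader, since the exclusion list does not state them. And the merging of stopping with quitting does not depend on how the exclusion list is read. Carrying a score forward fills the gap but does not supply the missing week-4 outcome, and the follow-up efforts are not extended to patients terminated under Study endpoints.

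**Conclusion.** The concern holds in a limited form. The exclusion wording permits removal of randomised patients although the schedule points to screening. Study endpoints treats stopping treatment as leaving the study and does not provide for further FSS, so some week-4 outcomes would be earlier scores, for reasons that may depend on arm and outcome. The ITT comparison is weakened but remains possible.

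The size of any bias cannot be computed from the documents. The range of 0.10–0.35 SD holds only if 10–20% are removed from one arm for outcome-related reasons (correlation 0.5 to 1) while losses in the other arm are unrelated to outcome. No section states such a removal, and the 20% dropout allowance in Sample size is a planning figure, not evidence of it. The change is still worth making, because it closes a route to bias at little cost.

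**What to change.** 1. In Eligibility criteria, limit the compliance and data-completeness exclusions to facts known before randomisation.
2. State that ITT contains all randomised patients in their allocated arm. Use compliance and concomitant-drug use after randomisation only to define the per-protocol set.
3. In Study endpoints, separate stopping stimulation from leaving the study. Continue the weekly FSS to week 4 for every randomised patient unless consent to assessment is withdrawn.
4. Reconcile Eligibility criteria, Basic treatments, Table 1, Study endpoints and Statistical analysis on medication and stopping. Which drugs are allowed and when treatment stops are clinical matters, and no rule is proposed here.

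The cost is protocol wording and a few more questionnaires. The per-protocol set may become smaller relative to ITT.
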